#### 6.1.4. Secondary outcomes

The secondary outcomes are presented descriptively and compared exploratively. The recurrences are visualised using Kaplan-Meier curves.

Complications are compared in the as-treated collectives.

#### 6.1.5. Determination of the number of cases

First endpoint: Pain: Measurements of pain intensity using VAS are known to show high variability. Postoperative values show standard deviations (SD) of 1.5 - 2.0 points, while in follow-up examinations the mean values as well as the dispersion tend to be lower (SD 1.0 - 1.5). A larger proportion of patients will also have no pain at follow-up. In the present study, we expect this to be the case for about half of the hernias for both materials. Patients with pain mostly report intensities  $<5$  points. An expected difference of one point is therefore considered too large. A difference of 0.5 points is therefore planned here. With an SD of 1.5 points, this would mean a reduction of one third of the standard deviation. The required number of cases

to detect such a difference (paired t-test; power 90 %;  $\alpha=0.025$ ) would be 114 hernias per group, i.e. 114 patients. As a non-parametric rank test is planned for the analysis, an additional 15% is added to the number of cases, i.e. 131 hernias per group, or 131 patients.

The second endpoint "recurrence" is a non-inferiority hypothesis. A recurrence rate of approx. 5 % is expected over a period of two years (synthetic meshes). The maximum acceptable difference to the recurrence rate for the biological meshes is +3 %, i.e. a maximum recurrence rate of 8 %. If both meshes have the same recurrence rate (e.g. 5 %), then 203 cases are required to rule out a difference of more than 3 %, i.e. the 95 % confidence interval around 0 % is then [-3; +3]. If the recurrence rate for the biological meshes is 1 % higher than for the synthetic meshes, then 451 cases would be required for a 95 % confidence interval of +/- 2 %, i.e. the confidence interval around the difference of +1 % would then be [-1; +3]. This means that a difference > 3 would also be outside the confidence interval. As this is a one-sided question, a difference > 3 % can only be achieved with a  $p<0.025$ .

Thus, the second endpoint (recurrence) requires a larger number of cases ( $n=451$ ). If one also assumes a follow-up loss of approx. 10 %, this figure increases to a total of 496 people (with bilateral hernias).

The number of patients to be screened is 10% higher:  $n=546$ .

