## II. Synopsis

|                                                       |                                                                                                                                                                                                                                       |
|-------------------------------------------------------|---------------------------------------------------------------------------------------------------------------------------------------------------------------------------------------------------------------------------------------|
| Sponsor:                                              | Witten/Herdecke University
[name]
[name]
represented by:
Centre for Clinical Studies at Witten/Herdecke University
[name]
[name]                              |
| Head of the clinical trial:                           | [name]. med. [name]
Viszeral-, Gefäß- und Transplantationschirurgie, Klinikum Köln
Merheim, [name]
[name]
[contact]                                            |
| Title of the clinical trial:                          | BIOLAP: Biological versus synthetic mesh in laparoscopic
hernia repair - a randomised multicentre, prospective, self-
controlled clinical trial                                                                                 |
| Indication:                                           | Bilateral primary inguinal hernias                                                                                                                                                                                                    |
| Type of examination,
study design/
methodology: | Prospective, intrinsically controlled, two-arm comparative
study of two CE-certified medical devices in the intended
indication with regard to efficacy                                                                         |
| Number of patients:                                   | 496 patients with bilateral inguinal hernia → 992 hernias                                                                                                                                                                             |

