#### 6.1.3. Primary outcomes

In this study, two primary endpoints are considered in parallel: pain intensity and recurrence. The total error of the first type ( $\alpha=0.05$ ) is distributed equally between the two endpoints according to a Bonferroni adjustment ( $\alpha=0.025$  in each case).

Pain intensity is recorded at 6 months after the operation using a visual analogue scale (VAS; 0-10 points) and tested for difference. Two pain values are recorded for each patient, separately for the left and right groin area. This means that dependent data is available. As experience shows that pain values are not symmetrically distributed, the evaluation is carried out non-parametrically with a rank test (Wilcoxon's rank sum test). The p-value is 0.025.

The second primary endpoint is the recurrence rate. The occurrence of a recurrence is recorded at several follow-up examinations over a period of 2 years after the procedure. A recurrence must be confirmed diagnostically. This endpoint will be tested for non-inferiority. It is expected that the recurrence rate with a biological mesh will be lower, the same or at most 3 % higher than the recurrence rate with a synthetic mesh. A range of  $\pm 3$  % is thus defined as still comparable. A 95 % confidence interval is determined for the observed difference in recurrence rates (biological - synthetic). If the value of  $+3$  % is not within this confidence interval, the biological mesh is considered non-inferior. Non-inferiority is a one-sided question. The 95 % confidence interval here corresponds to a one-sided question with a p-value of 2.5 %, as required by the Bonferroni correction.

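### The 203 and 451 cases for recurrence hold only if about 4.7% of patients are discordant (within-patient correlation about 0.50 to 0.55), which the protocol never states; power at a true +1 point is about 50% at best under that assumption

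*Protocol*

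**What the plan says.** Recurrence at two years is one of two primary endpoints and is tested for non-inferiority on the difference biological minus synthetic. Each patient contributes one groin to each mesh, so the data are paired.

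The planning inputs in section 6.1.5 are:

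- Synthetic rate: "A recurrence rate of approx. 5 % is expected over a period of two years (synthetic meshes").
- Margin: "The maximum acceptable difference to the recurrence rate for the biological meshes is +3 %, i.e. a maximum recurrence rate of 8" percent.
- Equal rates: "then 203 cases are required to rule out a difference of more than 3" points.
- Biological mesh 1 point worse: "then 451 cases would be required for a 95 % confidence interval of +/- 2" points, so that "the confidence interval around the difference of +1 % would then be [-1; +3"].
- Loss to follow-up: with about 10% added to 451, "this figure increases to a total of 496 people". The Synopsis repeats this as "496 patients with bilateral inguinal hernia".

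Section 6.1.3 sets the error level: "The 95 % confidence interval here corresponds to a one-sided question with a p-value of 2.5 %, as required by the Bonferroni correction".

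Section 6.1.5 plans pain at 90% power, which needs 131 patients. It states no power for recurrence, and no correlation between a patient's two sides, no share of discordant patients and no variance formula.

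**The concern.** The width of an interval for a paired difference depends on how many patients recur on one side only. Both kinds of discordant patient count: synthetic side only and biological side only. The protocol gives the two marginal rates but nothing that fixes this share. Even so, it gives exact case numbers and exact limits.

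If those limits do not follow from the stated inputs, the precision claimed for the endpoint that sets the trial size is unsupported. The recurrence half of the trial's aim rests on it.

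**Working it through.** **Inputs.** Synthetic rate p_s = 0.05. Biological rate p_b = 0.05 or 0.06, so d = 0 or 0.01. Margin 0.03, z = 1.96, n = 451 (sections 6.1.3 and 6.1.5). The correlation phi is not in the protocol and is varied here as an assumption.

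**Formula.** For n pairs with discordant share psi, the variance of the observed difference is (psi - d²)/n. For half-width w, n = 1.96² × (psi - d²)/w².

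**Reproducing the protocol's figures**

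- Equal rates, w = 0.03, psi = 0.05 × 0.95 = 0.0475: 3.8416 × 0.0475 / 0.0009 = 202.7, i.e. 203.
- +1 point, w = 0.02, psi = 0.05 × 0.94 = 0.0470: 3.8416 × (0.0470 - 0.0001) / 0.0004 = 450.4, i.e. 451.

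Both match to the integer with a total discordance of about 4.7%.

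**Independent sides**

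- 5% vs 5%: psi = 2 × 0.05 × 0.95 = 0.0950, so n = 405.5, i.e. 406.
- 5% vs 6%: psi = 0.05 × 0.94 + 0.06 × 0.95 = 0.1040, less 0.0001 = 0.1039, so n = 997.9, i.e. 998.

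**Correlation implied by the stated numbers.** The variance per pair is V = p_s(1-p_s) + p_b(1-p_b) - 2 × phi × sqrt[p_s(1-p_s) × p_b(1-p_b)].

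- 203: phi = (0.0950 - 0.0475) / (2 × 0.0475) = 0.50.
- 451: V must be 451 × 0.0004 / 3.8416 = 0.0470. Since sqrt(0.0475 × 0.0564) = 0.0518, phi = (0.1039 - 0.0470) / (2 × 0.0518) = 0.55.

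At phi = 0.55, the share recurring on both sides is 0.0030 + 0.55 × 0.0518 = 0.0315. So 0.0315 / 0.05, about 63%, of patients with a synthetic-side recurrence would also recur on the other side.

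**What 451 pairs deliver.** SE = sqrt(V/451), half-width = 1.96 × SE, power = Phi((0.03 - d)/SE - 1.96).

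| phi | Half-width at +1 (points) | Expected interval at +1 | Power at +1 | Power at equal rates |
|---|---|---|---|---|
| 0 | 2.97 | -1.97 to +3.97 | 26% | 54% |
| 0.3 | 2.49 | -1.49 to +3.49 | 35% | 70% |
| 0.5 | 2.11 | -1.11 to +3.11 | 46% | 83% |

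Worked line for phi = 0 at +1: SE = sqrt(0.1039/451) = 0.01518; 0.02/0.01518 - 1.96 = -0.64; power 26%. Simulation of the paired Wald interval at phi 0, 0.2 and 0.5 agreed with the formula to within one percentage point.

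**If the stated interval were right.** Half-width 0.02 means SE = 0.02/1.96. Then (0.03 - 0.01)/SE - 1.96 = 0, and power is Phi(0) = 50%.

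**Allowance for loss.** 451 × 1.1 = 496, but 496 × 0.9 = 446; keeping 451 after 10% loss needs 451/0.9 = 502. At 446 pairs, power changes by less than one point.

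**The case against.** The strongest defence is that zero correlation is an extreme case. Both groins belong to one patient and are repaired in one operation with the same technique, so some positive correlation is plausible. This stands, and it is why a range is shown. It does not rescue the stated figures, because they need 0.50 to 0.55 specifically and the protocol gives no reason for such a value.

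Several stronger readings are tempting but are not supported:

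- **Power is 26% to 54%.** Those are the zero-correlation values for two different true differences. Over phi 0 to 0.5, the ranges are 26-46% at +1 and 54-83% at equal rates.
- **A promised power is missed.** No power is stated for recurrence, so none is contradicted. Sizing by interval width is a design choice; that it gives about 50% power at +1 is a criticism of the design, not an arithmetic slip.
- **Non-inferiority will probably fail even for an acceptable mesh.** That is true at +1 for phi up to 0.5, but not at equal rates. Section 6.1.3 also allows for a lower biological rate: at 4% vs 5% with independent sides, the same formula gives SE 1.38 points and about 83% power.
- **A particular wrong formula was used.** The match to one discordant cell is exact, while a one-proportion formula at 5% gives 203 but 457 for the second figure. The derivation is still inferred. What can be shown is the discordance that the figures require.
- **The loss allowance is a material error.** It is not. Section 6.1.5 says approximately 10%, and section 4.4 replaces patients excluded before observation starts and continues until enough analysable patients are reached.

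**Conclusion.** The point holds as a fault in section 6.1.5. The stated case numbers and intervals do not follow from the stated rates without an unstated within-patient correlation of about 0.50 (203) to 0.55 (451). At any lower correlation, 451 pairs give a wider interval at +1, and its expected upper limit lies above the margin: +3.97, +3.49 and +3.11 at phi 0, 0.3 and 0.5. Separately, the +1 scenario that fixes the sample size has about 50% power at best for any correlation up to 0.55.

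The results rest on the protocol's 5% and 6% rates, a normal-approximation interval, and the one-sided 0.025 level of section 6.1.3. The Synopsis describes a one-sided 95% interval. Taken literally, that would give 37% power at +1 and 66% at equal rates with independent sides.

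**What to change.** Keep 496 patients and revise section 6.1.5:

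1. State the assumed discordant-pair rate or within-patient correlation, with its basis.
2. Replace the 203 and 451 statements and their intervals with the half-width and power that 496 patients (about 446 to 451 evaluable) deliver in both scenarios over a plausible correlation range. At 446 pairs and phi 0 / 0.3 / 0.5, this is 2.99 / 2.50 / 2.12 points and 26% / 35% / 46% power at +1, and 2.86 / 2.39 / 2.02 points and 54% / 69% / 83% power at equal rates. The justification for 496 then rests on the precision it delivers.
3. State that the recurrence endpoint has about 50% power or less at a true +1 point.
4. As a minor correction, note that 496 leaves about 446 after 10% loss.

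The protocol need not name an interval method for this purpose; that can be left to the SAP. The cost is a change of wording and less favourable stated precision. No extra patients and no change in conduct are needed.

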## **7. Use of the data and publication**

### **7.1. Reports**

#### **7.1.1. Interim reports**

No interim reports are planned.

#### **7.1.2. Final report**

The ethics committee will be informed of the termination of the clinical trial within 90 days.

Within one year of completion of the clinical trial, the summary of the final report on the clinical trial covering all significant events of the trial is submitted to the responsible ethics committee.

### **7.2. Publication**

It is planned to present the results of the clinical trial in a scientific journal and/or at German and international congresses in due course and after mutual agreement with the LKP. In principle, preference should be given to publication of the clinical trial as a whole. The "Uniform requirements for manuscripts submitted to biomedical journals (International Committee of Medical Journal Editors" (ICMJE) [JAMA 1997;277:927-34]) are taken into account.

Registration of the clinical trial in a public register in accordance with the recommendations of the ICMJE is also planned (see also 5.3).

For all publications, data protection is maintained for all data of study participants as well as for the data of participating investigators. The success rates and individual results of the participating trial centres are only known to the sponsor.

Publication or presentation of the results of this clinical trial, including publication or presentation by a single trial site, is subject to prior acknowledgement and prior comment and approval by the sponsor.

By signing the declaration of participation, the investigator agrees that the results of this clinical trial may be submitted to national and international regulatory and supervisory authorities, the German Medical Association, the National Association of Statutory Health Insurance Physicians and the health insurance funds. At the same time, the investigator agrees that his/her name, address, qualifications and the extent of his/her participation in the clinical trial may be disclosed in this context.

In the case of publications, support from the ZKS-UW/H is indicated. Where applicable, contributors to ZKS-UW/H projects are listed as co-authors. If the contributors are not co-authors of the article, they are named in the acknowledgements. A copy of all project publications must be made available to the ZKS-UW/H.

## **8. Changes to the study protocol**

In order to ensure largely comparable conditions in all trial sites and in the interests of proper data evaluation, no changes are planned to the agreed study conditions laid down in the study protocol. In exceptional cases, however, changes to the trial conditions are possible. These will only be made after mutual agreement between the sponsor, the sponsor representative, the LKP and the biometrician as well as all signatories (authors) of this protocol.

This does not apply to changes to the protocol that must be made directly for the safety of the patient.

Any change to the study procedures provided for in the protocol must be made in writing, stating the reasons for the change, and must be signed by all authors of the protocol (amendment).

Subsequent changes are submitted to the Ethics Committee for review and, if they concern changes that affect patient safety, data quality and/or data protection, are only implemented after the Ethics Committee has issued an opinion. This does not apply to changes that are necessary to avert immediate danger.

